## Abstract

**Background:**

A community-led oral health service for Aboriginal people in Central Northern NSW identified the need for oral health promotion, as well as dental treatment; in three remote communities with limited access to dental services. A three-stage plan based on the Precede-Proceed model was used to develop a school-based preventive oral health program. The program will be piloted in three schools over 12 months aimed at improving the oral health of local Aboriginal children.

**Methods:**

The proposed program includes four components: daily in-school toothbrushing; distribution of free fluoride toothpaste and toothbrushes; in-school and community dental health education and the installation of refrigerated and chilled water fountains to supply a school water bottle program. Primary school children will be issued toothbrushing kits to be kept at school to facilitate daily brushing using a fluoride toothpaste under the supervision of trained teachers and/or Oral Health Aides. School children, parents and guardians will be issued free fluoride toothpaste and toothbrushes for home use at three-monthly intervals. Four dental health education sessions will be delivered to children at each school and parents/guardians at local community health centres over the 12 month pilot. Dental education will be delivered by an Oral Health Therapist and local Aboriginal Dental Assistant. The program will also facilitate the installation of refrigerated and filtered water fountain to ensure cold and filtered water is available at schools. A structured school water bottle program will encourage the consumption of water. A process evaluation will be undertaken to assess the efficiency, feasibility and effectiveness of the pilot program.

**Discussion:**

The proposed program includes four core evidence-based components which can be implemented in rural and remote schools with a high Aboriginal population. Based on the Precede-Proceed model, this program seeks to empower the local Aboriginal community to achieve improved oral health outcomes.

**Trial registration:**

TRN: ISRCTN16110292 Date of Registration: 20 June 2018.

## Background

Dental caries is a serious problem for Australian Aboriginal children [1]. For example, Aboriginal children living in New South Wales (NSW) experience on average 2.64 decayed, missing or filled teeth (dmft/DMFT) due to dental caries. This is near double the dmft/DMFT rate of 1.54, experienced by non-Aboriginal children in NSW [2]. When left untreated, dental caries can cause severe pain, and negatively impact a child’s quality of life, ability to concentrate at school, and capacity to eat, speak and socialize without embarrassment [3].

Improving the oral health of Aboriginal children is a priority in the Oral Health 2020: A Strategic Framework for Dental Health in NSW [4], and the NSW Aboriginal Oral Health Plan [5]. It is essential that strategies aimed at improving the oral health of Aboriginal children are sustainable, supported by the local Aboriginal community and culturally competent [6].

Culturally competent health promotion programs for Aboriginal people should be developed in consultation with Aboriginal communities and designed to meet the needs of specific communities [5]. Additionally, they should be culturally and linguistically appropriate, evidence-based, sustainable, implemented in collaboration with communities and evaluated [7]. In rural and remote communities, programs that solely rely on the input from dental professionals are often not sustainable given the general shortage of qualified professionals [4]. Therefore, prevention programs that can be delivered by the local Aboriginal community are likely to be more sustainable and suitable for the needs of that population.

In 2013, Aboriginal Elders in Central Northern NSW, identified three Aboriginal communities that had extremely limited access to dental services and needed preventive oral health care programs. Subsequently, the Poche Centre for Indigenous Health and the Centre for Oral Health Strategy were invited into these communities to work in partnership with the local Aboriginal community to introduce sustainable dental services and preventive oral health care programs for Aboriginal people in the region [8] In 2014, a community-led oral health service was established, which provides comprehensive dental treatment for Aboriginal people in Central Northern NSW. The service operates using clinicians who have relocated to the region and local Aboriginal people who have been trained and employed as dental assistants. Portable dental equipment is used to provide dental treatment to Aboriginal children and adults from schools and local community health centres. The local Aboriginal community still however, maintained the need for preventive oral health care programs to be implemented alongside dental treatment provided in schools and community health centres.

In response to the community’s request for preventive oral health care programs, a three-stage plan based on the Precede-Proceed model of health program planning was used to develop a sustainable, community-led preventive oral health program (Fig. 1).

**Fig. 1 Fig1:**
[figure not shown]
Application of Precede-Proceed model for health promotion planning to plan and implement oral health promotion in three rural and remote communities in NSW

The Precede-Proceed model was used as it is a popular planning tool for population health programs [9]. It consists of a series of phases to assist researchers plan, design, implement and evaluate health programs. The first set of phases (PRECEDE) includes planned assessments to inform the design of the health program. The second set of phases (PROCEED) involves implementing a health program based on information learnt from the PRECEDE phases [10].

Guided by the Precede-Proceed model, Stage 1 included an epidemiological assessment of all Aboriginal children aged 5–12 years enrolled in local schools as well as an educational and ecological assessment of the community to determine predisposing risk factors and reinforcing and enabling factors to inform a targeted oral health program. The number of decayed, missing and filled teeth were recorded as well as baseline oral health knowledge and oral hygiene practices of children, parents/guardians, school staff and health workers.

The baseline data collected as part of Stage 1 data provided valuable planning information. The majority of children (87.5%) had untreated dental caries. The mean number of decayed primary teeth (dt) was 4.1 and the mean number of decayed permanent teeth (DT) was 0.7, indicating a clear need for dental treatment and education to prevent dental disease [11].

Ecological and educational assessment of the community identified four predisposing risk factors associated with an increased risk of developing dental caries:Low levels of tooth brush ownershipInfrequent daily toothbrushing with a fluoride toothpasteFrequent sugar consumptionHigh intake of sugar-sweetened beverages rather than drinking tap water

Based on the risk factors identified, the following oral health promotion strategies for Aboriginal children living in Central Northern NSW were developed, namely: increasing fluoride use through daily toothbrushing; ensuring safe and refreshing tap water is accessible to encourage the consumption of water rather sugar sweetened beverages; providing culturally competent oral health and nutrition education; and providing training programs to build capacity of the local Aboriginal community and existing health workforce to ensure oral health promotion is led and supported by the community.

The results of Stage 1 and proposed oral health promotion strategies were presented in a leaflet and also verbally reported back to the local Aboriginal people at an open community forum (locally known as a community ‘yarn up’) which is held to discuss local issues and events. The ‘yarn up’ included local Aboriginal Elders, teachers and school principals from the three local schools and representatives from the Poche Centre for Indigenous Health. The strategies were well-received at the ‘yarn up’ and members verbally agreed to the development of an oral health promotion program to be implemented in each of the schools in the three communities; which was later formalised in writing. This led to Stage 2 and thus the ‘implementation phase’ of the Precede-Proceed model.

Stage 2 involved developing a school-based oral health promotion program based on the findings of Stage 1. The program includes:Daily in-school toothbrushingDistribution of free fluoride toothpaste and toothbrushes to children and familiesIn-school and community dental health educationInstallation of refrigerated and chilled water fountains to supply a school water bottle program

The four components are based on existing programs which have shown to be effective in other Aboriginal communities [6, 12], and utilising high quality systematic reviews [13]. This study protocol describes the components of the proposed school-based program and evaluation protocol to determine the feasibility, efficiency and effectiveness of the strategies to control dental caries in Aboriginal children living in rural and remote communities in NSW.

The aim of the program is to improve the oral health of Aboriginal children by promoting daily toothbrushing using fluoride toothpaste, increasing oral health knowledge and encouraging the consumption of water to reduce the reliance on sugar-sweetened beverages.

Stage 3 will pilot the proposed program for 12 months in three schools in Central Northern NSW that enroll a high proportion of Aboriginal children. The process evaluation to be undertaken at the completion of the pilot, is based on the Precede-Proceed model for process evaluation (Phase 6) and will determine the program’s feasibility, efficiency, effectiveness and overall satisfaction of the participating communities.

## Methods

### Daily in-school toothbrushing with a fluoride toothpaste

Daily in-school toothbrushing will be implemented in all Kindergarten to Year 6 (primary) classes in the three schools.

At the commencement of the pilot, all children enrolled in Kindergarten to Year 6 will be issued with a toothbrushing kit. This kit will be labeled for each child and kept at school for daily toothbrushing. It includes a toothbrush, 1000 ppm fluoride toothpaste and hard plastic storage case for the toothbrush and paste.

Children will brush their teeth at school once per school day under the supervision of a trained teacher and/or Oral Health Aide. The program will allow the school to choose which combination will work at their school, whether this will be the existing classroom teacher, the introduction of an Oral Health Aide or a combination of the two. This approach will be used as the program has been designed to be led and implemented by the local community. The Oral Health Aide must be a local Aboriginal person to promote a culturally safe environment for children to brush their teeth at school, this may include providing individual children with support to brush their teeth. They will be employed by the school for 1 h per day and will assist the classroom teachers to implement the program by supervising toothbrushing.. The role of an Oral Health Aide was incorporated into the design of this study as a significant barrier to in-school toothbrushing programs is the demands on a teacher’s time [6]. It is based on the Children’s Oral Health Initiative (COHI) in Canada which utilizes ‘COHI Aides’ to support oral health promotion activities and provide oral health education [14]. Teachers and Oral Health Aides will receive a NSW TAFE skillset in Infection Control (HLTIN30IC) and First Aid (HLTAID003) to ensure they can supervise in-school toothbrushing safely.

All labeled toothbrush cases will be stored in a ventilated carrier next to the sink in each classroom and a replacement toothbrushing kit will be issued to each child every three months which will coincide with the commencement of each new school term.

The following outcomes will be used during the process evaluation to measure the reach and efficiency of daily in-school toothbrushing;At least 70% of Aboriginal children enrolled in the school have consented to participate in the program90% of children with consent to participate will brush their teeth at least 170 out of the 200 school days80% of children with consent to participate are continuing to brush their teeth each day at school after six monthsTeacher support for the program both at the time of commencement and six months later is positive.

### Distribution of free fluoride toothpaste and toothbrushes to communities

A strategic approach will be used in this program to distribute free fluoride toothpaste and toothbrushes to communities on a three-monthly basis to encourage the social norm of toothbrushing.

This approach will include:All children who participate in daily in-school toothbrushing will receive a second toothbrushing kit every three months to take home for home useSenior school children (Years 7–12) will receive a toothbrushing kit every three months to take home for home useParents/guardians at three-monthly intervals will receive free 1000 ppm fluoride toothpaste and toothbrushes every three months during dental health education sessions.

### In-school and community dental health education

Dental health education sessions will be delivered to school children and parents and guardians on a three-monthly basis over the pilot period to encourage the uptake of oral hygiene resources which will be distributed.

At the commencement of each new school term (three-monthly basis), a half-hour dental health education session will be delivered to children at each school. Therefore, a total of four sessions will be delivered at each school over the pilot period. Topics covered will be: encouraging brushing twice daily with fluoride toothpaste, restricting sugar intake and encouraging the consumption of water.

Parents/guardians will receive dental health education sessions at the local community health centre every three months (total of four sessions over 12 months). Topics will be: encouraging brushing twice a day with a fluoride toothpaste, demonstrating toothbrushing using a mouth model, restricting sugar intake and encouraging the consumption of water and information on seeking regular dental care. All education sessions will be delivered by an Oral Health Therapist and a local Aboriginal dental assistant.

Dental health knowledge and oral hygiene practices of children and parents/guardians will be collected following the completion of the pilot using the interviewer-assisted questionnaires which were used to collect baseline data in Stage 1. Results will be compared to baseline data to assess the impact of dental health education and the provision of free oral toothbrushes and toothpaste.

The following outcomes will be used during the process evaluation to measure the impact of dental health education and the provision of free oral toothbrushes and toothpaste:90% of Aboriginal children have a toothbrush and toothpaste at home90% of Aboriginal children brushed their teeth in the last 24 h70% of parents and/or guardians are satisfied with the toothbrushing program70% of parents and/or guardians assist their children to brush their teeth each nightA 70% increase in dental health knowledge specifically relating to the importance of the primary dentition, prevention of tooth decay and the effects of giving a baby a bottle of milk to bed.

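### The brushing criterion for education and home supplies counts any brushing in 24 hours, below the twice-daily message taught, and the supervised school session can meet it on its own

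*Protocol article*

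**What the plan says.** All places are in the Protocol article.

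- **What is taught** (Methods, In-school and community dental health education). The children's topics are "encouraging brushing twice daily with fluoride toothpaste, restricting sugar intake and encouraging the consumption of water". Parents and guardians receive the same messages, with a brushing demonstration and "information on seeking regular dental care". The stated purpose of the sessions is "to encourage the uptake of oral hygiene resources which will be distributed".
- **What is scored** (same section). Five outcomes are set "to measure the impact of dental health education and the provision of free oral toothbrushes and toothpaste". Two concern brushing itself: 90% "of Aboriginal children brushed their teeth in the last 24 h", and 70% of parents or guardians helping with brushing every night. The others are that 90% "of Aboriginal children have a toothbrush and toothpaste at home", that 70% "of parents and/or guardians are satisfied with the toothbrushing program", and a 70% "increase in dental health knowledge specifically relating to the importance of the primary dentition, prevention of tooth decay" and related topics.
- **What happens at school** (Daily in-school toothbrushing with a fluoride toothpaste). Children brush once on each school day under supervision. This component has its own targets, including at least 70% consent and 80% of consented children still brushing daily at school after six months.

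**The concern.** The criterion is meant to show whether education and home supplies changed behaviour, but it has two weaknesses. First, it is set at one brushing when the lesson is two, so a child who has not taken up the message still counts. Second, it does not say where the brushing took place. If the 24-hour window includes a school session, the supervised brushing meets it whatever happens at home. The result would then partly repeat the school register while being reported under education and supplies.

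At stake is the reading of a 90% result. It could mean that home brushing is now common, or only that the school sessions were well attended, and the criterion cannot tell these apart.

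**Working it through.** The article gives no sample size, power or test for this item, and questionnaire responses are analysed descriptively, so there is no stated figure to reproduce. The check asks how little twice-daily or home brushing is compatible with the targets being met.

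**Inputs.** Brushed in the last 24 hours: 0.90. Nightly parental assistance: 0.70. Still brushing daily at school at six months: 0.80 of consented children. Consent: at least 0.70.

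**Assumptions.** The window covers a school day with the sessions still running. Only consented children brush at school. There is one assisted child per parent, and all shares refer to the same children.

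**Step 1: the 24-hour item alone.** One brushing is enough, so the minimum share brushing twice is 0%. The minimum share brushing at home is also 0% whenever consent × school participation is at least 0.90.

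**Step 2: how far school brushing goes at the program's own targets.**
- Full consent: 1.00 × 0.80 = 0.80, leaving 0.90 − 0.80 = 10 percentage points to come from home brushing.
- 70% consent: 0.70 × 0.80 = 0.56, leaving 0.90 − 0.56 = 34 points.

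At those minimum targets, school brushing supplies most of the 90% but not all of it. Meeting the target with no home brushing requires participation above them.

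**Step 3: add nightly assistance.** One assisted evening brushing satisfies both brushing criteria. At least 70% then brush at home, but the minimum share brushing twice is still 0%.

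**Step 4: add the school continuation target.** School and evening brushing are separate events, so the lower bound on children doing both is max(0, a + b − 1).
- Full consent: 0.70 + 0.80 − 1 = 0.50.
- 70% consent: 0.70 + 0.56 − 1 = 0.26.

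Even with the school target added, twice-daily brushing on a school day is guaranteed for only 26% to 50% of children.

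**The case against.** **The lower bar has a rationale.** The Background names infrequent daily brushing as a Stage 1 risk factor, and the Discussion ties brushing at least once a day to less caries. A pilot may teach an ideal and set a more modest benchmark. This stands as a reason to keep the once-or-more figure. It does not answer the second weakness, that the school session can supply that brushing.

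**Home behaviour is measured elsewhere.** Nightly assistance partly scores home brushing, and oral hygiene practices are collected again with the Stage 1 questionnaires and compared with baseline. This also stands: what is lacking is a suitable threshold, not all measurement. The baseline comparison has no target for twice-daily brushing.

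**The sessions aim at uptake of supplies.** That is their stated purpose, and having a brush and paste at home scores it directly. So it would be wrong to say that the list misses what the sessions were for.

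**The interviews come at the end of the pilot.** If school brushing has stopped by then, it cannot fill the window. The article does not say whether it continues. In that case only the gap between once and twice remains.

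**Broader readings go too far.** A reader might infer that education alone is credited, but the list judges education and free supplies jointly. A reader might infer that sugar goes unscored, or that water is the only taught behaviour with a criterion. However, the School water bottle program section sets a 70% reduction in sugar-sweetened beverages, and Data collection includes diet change in the children's questionnaire. The visible lists have no criterion for dental visits, but the process evaluation table is not shown and the article is condensed, so an omission cannot be asserted.

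**Conclusion.** The point holds for one criterion. The 24-hour brushing item is lower than the message taught, and on a school day a brushing that belongs to another component can meet it. Together with nightly assistance, it can be met with 0% of children brushing twice a day. With the school continuation target added, the guaranteed share is 26% to 50%, given one child per parent, common denominators and a school-day window.

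Meeting the item with no home brushing at all is possible, but needs school participation above the program's minimum targets. If nightly assistance is also met, a substantial share of children do brush at home. These bounds show what the criteria permit; they do not predict the result. No figure in the article is wrong. The evidence does not support concluding that the evaluation as a whole ignores the taught behaviours. This is a modest correction, worth making because it is nearly free.

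**What to change.** In the outcomes listed under In-school and community dental health education:

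1. Score the share of Aboriginal children who brushed at least twice in the last 24 hours. An alternative is at least once outside the supervised school session. For a child who took part in one school session within the window, the two wordings give the same answer. For a child who did not, the twice item is stricter, so the choice should be stated.
2. Report the share who brushed at least once alongside, for comparison with Stage 1.
3. Decide before the interviews whether 90% is still the right target for the new item, and restate it if not.
4. Optionally, report the diet-change answers already planned under Data collection for sugary foods as well as drinks, as a descriptive result without a target.

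The cost is one reworded questionnaire item and criterion, with no new contacts. The figure will look less favourable than the once-or-more figure. If Stage 1 did not record brushing frequency, the new item has no baseline and can only be reported as an end-of-pilot level.

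### The comparison with Stage 1 gives total change under the whole program in its setting, not the impact of education and free supplies

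*Protocol article*

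**What the plan says.** The protocol article's Methods section on in-school and community dental health education plans a follow-up of children and parents or guardians after the pilot, "using the interviewer-assisted questionnaires which were used to collect baseline data in Stage 1". It then says what the comparison is for: "Results will be compared to baseline data to assess the impact of dental health education and the provision of free oral toothbrushes and toothpaste". Five outcomes follow, introduced as measures of the impact of those same two components. They cover having a brush and paste at home (90%), brushing within the past 24 hours (90%), parent satisfaction (70%), parental help with brushing at night (70%) and a 70% increase in knowledge.

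The setting is a single group: "Stage 3 will pilot the proposed program for 12 months in three schools in Central Northern NSW". Under Data collection, questionnaire responses are to be analysed descriptively.

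Three other parts of the article describe influences on the same people over the same interval:

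- The Methods section on daily in-school toothbrushing has primary children brush once each school day under supervision, in all three schools.
- The Background describes a dental service: "In 2014, a community-led oral health service was established, which provides comprehensive dental treatment for Aboriginal people in Central Northern NSW". On where it works, it says: "Portable dental equipment is used to provide dental treatment to Aboriginal children and adults from schools and local community health centres". The community wanted "preventive oral health care programs to be implemented alongside dental treatment provided in schools and community health centres".
- The Background also reports feedback after the baseline survey: "The results of Stage 1 and proposed oral health promotion strategies were presented in a leaflet and also verbally reported back". This took place at an open community forum, before the program was developed and piloted.

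**The concern.** A before-after comparison in one group measures everything that changed between the two surveys. The article assigns that change to two of the four program components. The other components run over the same 12 months, and at least two influences outside the program could also move knowledge and brushing habits.

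What is at stake is the conclusion that others will draw. The Discussion hopes that the study will inform oral health promotion across NSW and Australia, and it stresses the shortage of dental professionals in remote areas. A community could read the result as showing that education and free supplies suffice, and then leave out supervised brushing. A community without a visiting dental service could expect the same change. The comparison as planned supports neither conclusion.

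**Working it through.** The plan gives no figure to reproduce here, so the check sets the passages side by side and adds one short calculation.

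**1. What the comparison measures.** For any knowledge or practice outcome,

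observed change = E + B + W + D + F + T,

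where E is education and free supplies, B is supervised school brushing, W is the water bottle program, D is the change in the dental service's influence between the two surveys, F is the feedback of Stage 1 results and T is any other trend over time. The plan observes the left-hand side only. With no comparison group, and no adjustment described in the article, E cannot be separated from the rest.

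**2. School brushing (B).** A child who brushed under supervision that day has brushed within the past 24 hours, whatever happened at home. The article's own targets in the toothbrushing section show how far the two overlap. The inputs are 70% of enrolled Aboriginal children consenting, and 90% of consented children brushing on at least 170 of 200 school days.

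- 170 / 200 = 0.85
- 0.90 × 0.85 = 0.765
- 0.70 × 0.765 = 0.5355

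If those targets were only just met, on an average school day at least 76.5% of consented children, or about 53.6% of enrolled Aboriginal children, would have brushed at school. This assumes that the 90% applies equally to Aboriginal children with consent, and it counts everyone else as zero. So a large part of the 90% target for brushing in the past day could be met without any home brushing. The figure shows overlap with the target. It is not a share of the change, because a child who brushes at school may also brush at home and the baseline percentage is not given.

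**3. Dental service (D).** The service dates from 2014 and Stage 1 is undated. The Background mentions the service before the three-stage plan, which suggests that it may already have been running at baseline. If so, part of its influence is in both surveys and cancels. Only a continuing or growing effect enters D. The article reports neither its presence nor its absence.

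**4. Feedback (F).** The leaflet and forum came after the Stage 1 survey, so F lies wholly inside the interval. The named attendees are Elders, teachers, principals and centre representatives. How many parents or children were reached is not stated.

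**5. Which outcomes are affected.**

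- *70% increase in knowledge:* defined as a change, so directly affected.
- *Hygiene practices compared with baseline:* affected. Brushing in the past day is the clearest case, because of step 2. Parental help at night is open to D and F, but school brushing does not meet it by itself.
- *Brush and paste at home:* supplied directly by the take-home kits, so crediting free supplies is reasonable.
- *Parent satisfaction with the program:* not a before-after measure, so not affected.

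**6. Size.** Without baseline questionnaire percentages, a date for Stage 1, figures on dental contact or the reach of the feedback, no term in step 1 can be bounded.

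**The case against.** The strongest reply is that this is the ordinary limit of a one-group pilot. The work is described as a process evaluation with descriptive statistics, no test or causal model is specified, and delivery alongside dental treatment is what the community asked for. That lowers the stakes. It does not change the text, which still speaks of impact and effectiveness and names two components as the cause.

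The second reply is that a service established in 2014 may be a constant background that cancels. This stands in large part, and it is why the service counts only for any continuing or growing effect. The feedback limb is also modest: survey results and proposed strategies are not hygiene instruction, and the reach is unknown. Neither reply touches school brushing, which starts with the pilot.

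The third reply is that four of the five outcomes are absolute targets. That is correct and it narrows the point, but the sentence on comparison with baseline covers knowledge and practices generally.

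The fourth reply is that the evaluation table and the questionnaire items are not shown, so dental contact may already be asked about. This also stands. The article cannot be faulted for omitting such items, and the proposal to add them is therefore conditional.

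**Conclusion.** The point holds as one of attribution. Followed as written, the plan would credit education and free supplies with change that may come partly from supervised school brushing, from the dental service or from the earlier feedback. It matters mainly for the 70% knowledge increase and the comparison of practices, and it is most visible for brushing in the past day.

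A reader might infer more: that the service and the feedback reached the same families, that both were new after baseline, and that the overstatement can be put in percentage points by treating the 87.5% of Stage 1 children with untreated caries as the share treated since. The documents do not support this. They show shared communities and types of setting, not person-level overlap. They do not date Stage 1. Need for treatment is not receipt of treatment, and the effect of a dental visit on brushing or knowledge is nowhere given. The contributions are plausible, but their size is unknown.

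The conclusion rests on the article as shown: three schools, all receiving the program, no comparison group described and descriptive analysis only.

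**What to change.** Reword the comparison sentence, and the line introducing the five outcomes, so that the result is described as *change since Stage 1 under the whole program, delivered alongside the dental service*, and not as the impact of education and free supplies.

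If the questionnaire does not already do so, add two short items for children and parents: contact with the dental service since Stage 1, and number of education sessions attended. The contact item should distinguish a treatment visit from an education session, because an Oral Health Therapist and a dental assistant deliver the sessions. Report the knowledge and practice outcomes by these two items, as description only.

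The cost is a narrower claim, two items and the extra descriptive reporting. The subgroups will be small and self-selected. Because the parent sessions also give information on seeking dental care, some dental contact may result from the program. The split therefore shows context and cannot recover a component effect.
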